## Abstract

**Background:**

Conservative surgery followed by breast and nodal irradiation is the standard loco-regional early breast cancer (BC) treatment for patients with four or more involved lymph nodes. However, the treatment strategy when fewer nodes are involved remains unclear, especially when lymphadenectomy has not been performed. Sensitive nodal status assessment molecular techniques as the One-Step Nucleic Acid Amplification (OSNA) assay can contribute to the definition and standardization of the treatment strategy. Therefore, the OPTIMAL study aims to demonstrate the feasibility of incidental irradiation of axillary nodes in patients with early-stage BC and limited involvement of the SLN.

**Methods:**

BC patients who underwent conservative surgery and whose SLN total tumour load assessed with OSNA ranged between 250–15,000 copies/µL will be eligible. Patients will be randomized to receive irradiation on the breast, tumour bed, axillary and supraclavicular lymph node areas (intentional arm) or only on the breast and tumour bed (incidental arm). All areas, including the internal mammary chain, will be contoured. The mean, median, D5% and D95% doses received in all volumes will be calculated. The primary endpoint is the non-inferiority of the incidental irradiation of axillary nodes compared to the intentional irradiation in terms of 5-year disease free survival. Secondary endpoints comprise the comparison of acute and chronic toxicity and loco-regional and distant disease recurrence rates.

**Discussion:**

Standardizing the treatment and diagnosis of BC patients with few nodes affected is crucial due to the lack of consensus. Hence, the quantitative score for the metastatic burden of SLN provided by OSNA can contribute by improving the discrimination of which BC patients with limited nodal involvement can benefit from incidental radiation as an adjuvant treatment strategy.

**Trial registration:**

ClinicalTrial.gov, NCT02335957; https://clinicaltrials.gov/ct2/show/NCT02335957

## Background

It has been shown that breast and nodal irradiation reduce mortality and disease recurrence in breast cancer (BC) patients [1]. Therefore, there is evidence supporting the use of adjuvant radiotherapy after conservative surgery. Since nodal irradiation increases survival rates, it is recommended in patients with four or more involved lymph nodes (LN) [2], as well as in patients with other types of locally advanced tumours with LN involvement [3]. A randomized clinical trial carried out by the British Columbia Cancer Agency, showed that the 20-year disease-free survival (DFS) of patients subjected to the combination of chemotherapy and radiation was 13% higher than that of the patients who were treated with chemotherapy alone [4]. Similar results were achieved in the DBCG 82 b&c trial showing a difference of 10% in the 15-year overall survival rate between the treatment combination and chemotherapy alone (39% vs. 29%, respectively) [5]. Furthermore, a study funded by the Canadian Cancer Society concluded that adjuvant radiation treatment of limited LN-positive patients (0–3 involved nodes) led to a decrease in disease recurrence [6]. However, there is no consensus on the recommendation of radiotherapy when the nodal involvement ranges between 1 and 3 LN [7].

Furthermore, this situation became even more unclear since Giuliano et al. demonstrated no significant benefit in loco-regional control with completion of axillary lymph node dissection (ALND) in comparison to no ALND in patients with 1–2 involved LN [8, 9]. On the other hand, AMAROS [10] and OTOASOR [11] trials demonstrated that nodal irradiation should be regarded as the recommended treatment for patients with few involved LN, instead of ALND. In line with their results, the Canadian trial NCIC-CTG MA20 [6] showed that local irradiation combined with regional irradiation improved the DFS as well as the loco-regional and distant control of the disease in high-risk patients with negative and with positive LN, mostly with 1 to 3 involved LN, while Poortmans et al. [12] demonstrated that the irradiation of the regional nodes in patients with limited axillary disease results in an increase of the DFS. Darby et al. [13] reported that, after breast-conserving surgery, the application of radiotherapy to the breast reduced mortality and the disease recurrence by half. Finally, a systematic review, which included more than 20,000 patients from 45 studies, concluded that breast irradiation reduced the loco-regional relapse even in patients without LN involvement [14]. Later on, the meta-analysis conducted by Budach et al. [15, 16] concluded that additional regional radiation to the internal mammary and medial supraclavicular LN improved overall and disease-free survival rates in stage I-III BC patients.

The uncertainty about the proper radiation therapy entails the need for a method that standardizes the choice of treatment and complements the limited diagnostic information [17–19], such as nodal involvement assessment. The OSNA (One-Step Nucleic Acid Amplification) assay provides a quantitative value of the metastatic burden of the sentinel lymph node (SLN) by measuring the mRNA expression of the tumour marker cytokeratin 19 (CK19) [20]. The OSNA assay not only provides automated and complete intraoperative analyses of the SLN but also standardized and reliable results for SLN metastatic status. The total tumour load (TTL), defined as the sum of the CK19 mRNA copies from all positive SLNs of the patient, entails a quantitative score that integrates both the metastatic burden and the number of involved SLN. The TTL score was proved to be an independent predictor factor of the axillary nodal status, where only 14.7% of patients with TTL beneath 15.000 copies/µl had other positive non-SLN [21]. Recently, the PLUTTO study results also proved its impact on the prognosis of BC patients [22].

Therefore, the OPTIMAL study (OPTimizing Irradiation through Molecular Assessment of Lymph node) aims to demonstrate the non-inferiority of incidental irradiation of axillary nodes in comparison to intentional irradiation in terms of the 5-year DFS of patients with early-stage BC and limited involvement of the SLN according to the OSNA quantitative score.

## Methods/design

### Study design

The OPTIMAL study is an open-label multicentre and international trial (NCT02335957) conducted in over 40 sites in Spain, Portugal, and Italy. Eligible patients will be randomized with a 1:1 allocation ratio to receive irradiation on breast, tumour bed, axillary and supraclavicular lymph node areas (intentional arm) or only on breast and tumour bed (incidental arm), as depicted in Fig. 1. Randomization by blocking within centres to minimize imbalance of treatments among centres will be performed using the online randomization software RANDI2 (www.dkfz.de; Heidelberg University) embedded in the electronic case record form (eCRF). All patients will have to provide their Informed Consent prior to the inclusion in the study.

**Fig. 1 Fig1:**
[figure not shown]
OPTIMAL-I study design. *BC* breast cancer, *CK19* cytokeratin 19, *mRNA* messenger ribonucleic acid, *SLN* sentinel lymph node, *TTL* total tumour load

### Eligibility criteria

#### Inclusion criteria

Older than 18 years oldFemale invasive ductal breast cancer patientsT1–T2 tumour stagePrevious treatment with breast-conserving surgery without axillary lymphadenectomyOSNA assayed SLN with a TTL within the 250–15,000 copies/µL rangeKarnofsky Performance scale Index ≥ 70%Written and signed Informed Consent

#### Exclusion criteria

Invasive lobular carcinoma and other histologic subtypesBilateral breast cancerMale breast cancer patientsPatients who underwent a mastectomy or ipsilateral dissection of axillary LNHaving received previous thoracic irradiationSystemic neoadjuvant therapy prior to surgeryContraindications to radiotherapy such as pregnancy or serious collagen disease.Other neoplasms and or any associated sever comorbidities that may interfere with the study

### Endpoints

#### Primary endpoint

The primary endpoint is the non-inferiority of incidental irradiation of axillary nodes in contrast to intentional irradiation, in terms of the 5-year DFS of patients diagnosed with early-stage breast cancer with limited involvement of the SLN treated with breast-conservative surgery without axillary lymphadenectomy.

#### Secondary endpoints

The secondary endpoints established were the following:Loco-regional tumour recurrence in the two treatment arms within the 5-year follow-up period.Distant tumour recurrence in the two treatment arms within the 5-year follow-up period.Acute toxicity induced by either the incidental or intentional radiation treatment.Chronic toxicity induced by either the incidental or intentional radiation treatment.Total irradiation dose (Gy) received in axillary levels I-III, supraclavicular fossa, and internal mammary chain volumes.

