#### Treatment planning

The treatment planning must be carried out on a 3D system with tissue heterogeneity correction and matrix resolution of 2.5 mm. Techniques in the supine position are allowed and the prone position is not allowed.*Breast* Tangent beam pair arrangement to encompass the whole breast is recommended, intending to minimize the total dose in the ipsilateral lung and heart. The treatment plan can be optimized with any dose compensation system, (virtual edges, mechanical wedges, automatic wedges, field-in-field IMRT and steep and shoot or sliding windows IMRT). The treatment will be performed with photons of 6 MV–15 MV. The isocenter will be located within the breast PTV in the experimental group and may be located outside the PTV if the single isocenter technique is being used in the control group. To minimize irradiated ipsilateral lung and heart volumes, collimator rotation and shield with multileaf collimator is allowed.*Tumour bed* Photons or electrons are allowed. Mini-tangential photon fields or single electron field (also mixed energies) can be utilised. The use of boluses can be considered if needed. Simultaneous integrated boost brachytherapy or intraoperative irradiation is also allowed if the dose contribution to the nodal areas can be calculated. The bolus can be used. The dose and fractionation choice is left at the discretion of the treating physician.*Node areas* In the control group, the treatment planning must be optimized to ensure that the nodal areas receive the prescribed dose (except for the internal mammary chain), minimizing the dose at the organs at risk. High tangent, AP/PA, conformational 3D and IMRT techniques are allowed. In the experimental group, treatment planning for nodal areas is not performed. The internal mammary chain will not be irradiated intentionally in any case.

An unplanned gap of up 3 days is acceptable. Longer non-planned interruptions should be compensated by hyperfractionation of the daily normal dose.

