### Data collection and analysis

#### Data collection

The study data will be recorded in an eCRF (OpenClinica®, LLC). The demographic and clinical data requested is depicted in Table 2. Acute and chronic toxicity will be recorded according to the Common Terminology Criteria for Adverse Events v4.0 (CTCAE) [24] criteria. Specific follow-up outcomes will be assessed and registered during the visits scheduled as stated in Table 1.

**Table 2 Tab2:** Data collected in the electronic case record form

Panel in eCRF	Data recorded
Informed consent	Date
I/E criteria	Yes; not
Demographic data	Age at inclusion; Menstrual State
Comorbidities	If yes: specify
Cancer Histology and Receptors, SLN OSNA	Tumour grade; Tumour size (maximum diameter); P53 (%); Ki67 (%); Lymphovascular infiltration; Ductal Ca in situ; % Estrogenic receptors; % Progesterone receptors; HER2 receptor status; OSNA TTL of SLN
Previous medication (Adjuvant therapy)	Drug; Start date; Stop date
Type of surgery	Tumour surgery; date; Margins
Randomization	Treatment randomly allocated; Randomization date
Radiotherapy intervention	Patient completed the allocated treatment (If no: main reason); Start date; End date; Treatment gaps (If yes, reason); Dose per volume (Mean; Median; D95; D5; Volume) in the breast, tumour bed, supraclavicular and axillary levels I-III, and Internal mammary chain
Co-medication	Drug; Start date; Stop date
Survival and disease recurrence	Date of follow-up visit (If not performed, reason); Local recurrence; Regional recurrence (If yes: nodal level); Distant recurrence (If yes: organ); Vital status (if dead: date and cause)
Image evaluation of local recurrence	Technique; Local recurrence (if yes: Maximum diameter)
Physical examination^a^	Palpable breast tumour (if yes: size, skin infiltration, inflammatory carcinoma, satellite lesions); Palpable axillary nodes (if yes: size); Palpable supraclavicular nodes (if yes: size); Node staging
Acute and chronic toxicity	CTCAE term; Grade; Start date; Stop date; Status (recovered w/o sequels; death)

*eCRF* electronic case record form, *OSNA* One-Step Nucleic Acid Amplification, *TTL* total tumour load, *SLN* sentinel lymph node, *CTCAE* Common Terminology Criteria for Adverse Events

^a^Physical examination is conducted at follow-up visits. It is also addressed at baseline and radiotherapy sessions to confirm the compliance of eligible criteria. If suspicious LNs are detected, the patient will discontinue the study

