#### Statistical analysis

Two sets of patients will be analysed: the intention-to-treat (ITT) group, which includes all randomized patients, to describe the baseline clinic-pathological patients’ characteristics; and the per-protocol subset, which includes patients who finish the intervention treatment as planned with all dosimetry data completed, for the endpoint. A descriptive analysis will be carried out reporting absolute and relative frequencies for all variables recorded and stratified by treatment group. Two analyses of the primary endpoint (disease-free survival rate) will be conducted. The confirmatory analyses will be carried out using a non-inferiority long-rank test in the ITT set of patients, which includes all randomized patients regardless of whether the treatment or follow-up are accomplished. A secondary explanatory analysis will be conducted in the per-protocol subgroup, which will include patients who will have finished the intervention treatment with all dosimetry data completed, by an adjusted Cox regression model using the covariates: centre, age at inclusion, tumour size, hormone receptor status, Her2 receptor status, and OSNA results. With regards to the secondary endpoints: the outcomes of loco-regional and distant recurrence will be analysed using the Cox approach, this time in the ITT set. Acute toxicity will be analysed by a chi-squared test comparing frequencies in both treatment groups. Chronic toxicity will be analysed by using Kaplan Meier curves and comparing them by a standard log-rank test. Interim analyses are planned when 85 events and 169 events will be reached.

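### Pooling in-breast with nodal recurrence dilutes the comparison of nodal failure, the outcome closest to the randomised difference; regional recurrence should be a separate secondary endpoint

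*Protocol article*

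**What the plan says.** Study design randomises patients "to receive irradiation on breast, tumour bed, axillary and supraclavicular lymph node areas (intentional arm) or only on breast and tumour bed (incidental arm"). Treatment planning confirms that the contrast is nodal: "In the experimental group, treatment planning for nodal areas is not performed". The same section says that the internal mammary chain is not irradiated intentionally in either arm.

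Secondary endpoints lists "Loco-regional tumour recurrence in the two treatment arms within the 5-year follow-up period" and, separately, distant recurrence. Statistical analysis assigns the model to the same two outcomes: "the outcomes of loco-regional and distant recurrence will be analysed using the Cox approach, this time in the ITT set". The abstract also speaks of "loco-regional and distant disease recurrence rates". None of these places names regional recurrence alone.

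Table 2, under Data collection, shows that the eCRF holds the components apart: "Local recurrence; Regional recurrence (If yes: nodal level); Distant recurrence (If yes: organ").

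**The concern.** If leaving out intentional nodal fields does harm, the most direct sign is recurrence in those nodes. In-breast recurrence should be similar by arm, because the breast and tumour bed are irradiated in both. Adding a component that is insensitive to the allocation moves the pooled hazard ratio toward 1. In a non-inferiority trial that movement reassures: a pooled loco-regional result that shows little difference could be read as evidence of nodal control when it mostly reflects breast events. The secondary endpoints include radiation dose to each nodal region, but no recurrence outcome for those regions.

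**Working it through.** The plan gives no figure for this point. Neither the 15% control recurrence rate (Sample size estimation) nor the 13 recurrences so far (Current status of the trial) is split by site. What follows is an illustration.

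**Inputs from the document:** 1,400 patients allocated 1:1, so 700 per arm; 5% yearly dropout; 5 years of follow-up.

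**Assumed:** 5-year regional rates of 1% versus 3%, or 1% versus 2% (intentional versus incidental); an in-breast rate of 2%, 3% or 5%, equal in both arms; two-sided 5% test; exponential times; full 5-year follow-up apart from dropout; no competing events.

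**Formulas**
- Hazard from a 5-year risk p: λ = −ln(1 − p)/5. Dropout hazard: η = −ln(0.95) = 0.0513 per year.
- Probability of an observed event: λ/(λ + η) × [1 − exp(−5(λ + η))].
- Pooled hazard: λ(in-breast) + λ(regional).
- Power (Schoenfeld), with d events in total: Φ(½√d × ln HR − 1.96).

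**Regional alone, 1% versus 3%.** λ = 0.00201 and 0.00609, so HR = 3.03. Expected events are 6.2 + 18.5 = 24.7. Then ½√24.7 × ln 3.03 = 2.76, and Φ(2.76 − 1.96) = 79%.

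**Pooled, in-breast 3%.** λ = 0.00609 + 0.00201 = 0.00810 versus 0.00609 + 0.00609 = 0.01218, so HR = 1.50. Events are 61.1. Then ½√61.1 × ln 1.504 = 1.59, and Φ(1.59 − 1.96) = 36%.

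| Assumed regional rates | Outcome | Events | HR | Power |
|---|---|---|---|---|
| 1% vs 3% | Regional alone | 24.7 | 3.03 | 79% |
| | Pooled, in-breast 2% | 48.9 | 1.68 | 44% |
| | Pooled, in-breast 3% | 61.1 | 1.50 | 36% |
| | Pooled, in-breast 5% | 85.3 | 1.33 | 26% |
| 1% vs 2% | Regional alone | 18.5 | 2.01 | 32% |
| | Pooled, in-breast 2% | 42.9 | 1.34 | 16% |
| | Pooled, in-breast 3% | 55.1 | 1.25 | 13% |
| | Pooled, in-breast 5% | 79.5 | 1.17 | 10% |

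**Wider range, without dropout.** For in-breast rates of 1–4%, control regional rates of 0.5–2% and a two- or threefold regional risk, power was 20–99% for regional alone and 6–95% pooled. Pooling lowered it in all 24 combinations.

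**Precision of a regional difference.** Ignoring dropout, the 95% half-width for 1% versus 3% is 1.96 × √[(0.01 × 0.99 + 0.03 × 0.97)/700] = 1.5 percentage points. For 1% versus 2% it is 1.3 points.

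**Would DFS catch it?** Suppose the whole 2-point rise carried into the primary endpoint, 15% versus 17%. Without dropout, SE = √[(0.15 × 0.85 + 0.17 × 0.83)/700] = 0.0196. The chance of declaring non-inferiority at a 5-point margin is Φ(0.03/0.0196 − z). That is 45% at one-sided 0.05 and 33% at one-sided 0.025, compared with 84% and 75% when the arms are equal. The article does not state alpha, so both levels are shown.

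**The case against.** Loco-regional recurrence is a conventional outcome, and the primary aim is DFS, not axillary control. The article contains no contradiction here, and a full protocol or SAP that is not shown may break the outcome into components. That limits the point: a reader might infer that the trial discards the nodal data or will never look at them, and the document does not support that. The data are collected. What stands is that the article does fix the recurrence outcomes to be compared, consistently, and the one nearest to the randomised difference is not among them.

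A reader might also infer that DFS non-inferiority would readily be met while nodal failure rises several-fold, because a 2-point rise is smaller than the margin. That goes too far. The confidence limit has to clear the margin, and at 15% versus 17% it would do so in only about 33–45% of trials before dropout. DFS is sensitive to such a rise, although it can still pass. Nor does the article list the events that make up DFS, so how nodal recurrence combines there with distant recurrence or death cannot be stated as fact.

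Equal in-breast recurrence is an expectation. Treatment planning lets the isocentre position differ by arm, so breast technique need not be identical.

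Finally, separating the outcome does not guarantee an adequate test. For regional rates of 0.5% versus 1%, regional-only power is 18% with about 9 events. This stands, and it is why the comparison should be framed as estimation.

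**Conclusion.** The concern holds as an improvement to the stated secondary endpoints, not as an error that undermines the primary analysis. The planned contrast is nodal, while the named recurrence outcomes are pooled loco-regional and distant. Provided in-breast recurrence is about equal by arm, the direction of the dilution is certain: the pooled hazard ratio lies nearer to 1 than the regional one. Its size cannot be taken from the documents. On the assumed rates, pooling lowers power from 79% to 44–26% (1% versus 3%) or from 32% to 16–10% (1% versus 2%). The main value of a regional outcome is an estimate with an interval for the quantity that the randomisation is meant to affect.

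**What to change.** In Secondary endpoints and Statistical analysis:

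- Add regional recurrence in axillary levels I–III and the supraclavicular fossa as a separate secondary endpoint, derived from the existing nodal-level field.
- Report its ITT 5-year cumulative incidence difference with a confidence interval beside the DFS result.
- Report in-breast recurrence and internal mammary recurrence separately. The internal mammary chain is intentionally irradiated in neither arm, so including it in the regional endpoint would bring back some of the dilution.
- Keep pooled loco-regional recurrence as listed.

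The cost is a change to the endpoint wording and one further analysis of data already collected, with no new visits or patients. The downside is few events and a wide interval, so the text should say that this endpoint is for estimation. It should be specified before any comparison of recurrence by arm is seen.

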### Radiation procedure

#### Volume contouring

All node areas from axillary levels I-III, the supraclavicular fossa and the internal mammary chain must be contoured in all patients regardless of the assigned arm following the guidelines of the Radiation Therapy Oncology Group [23]. The Clinical Target Volumes (CTV) will be delimited as stated below:*Breast* The CTV includes the whole breast’s soft tissues ranging from 5 mm below the skin surface to the deep fascia, excluding the muscle and underlying ribs. The posterior margin should not extend beyond the deep fascia or the edges of the visible/palpable breast in medial and lateral directions.*Tumour bed* The delineation of the tumour bed is only mandatory for patients who require a boost. It is strongly recommended to delimit the medial, lateral, superior, inferior, anterior and posterior margins of the surgical cavity at the time of the surgery, with clips or gold seeds. In the absence of implanted fiducial markers, the tumour bed may be localised if there is a well-defined seroma, considering visible changes in the computed tomography (CT) or by means of support from previous mammograms or magnetic resonance imaging. This volume shall be defined by drawing around the implanted markers and changes in the surrounding tissue architecture.*Supraclavicular* In the incidental arm, nodes will be contoured as part of the procedure whereas, in the control group, this will be hidden so as not to influence the dosimetric planning. The limits will be cranial edge (thyroid cartilage); caudal edge (clavicle head); medial edge (1 cm lateral to the lateral wall of the trachea excluding the thyroid); lateral edge (acromioclavicular joint); anterior edge (the sternocleidomastoid muscle and the clavicle); posterior edge (the trapezius muscle).*Axilla level III* In the incidental arm, nodes will be contoured as part of the procedure whereas, in the control group, this will be hidden to not influence the dosimetric planning. The limits will be the cranial edge (5 mm cranial to the axillary vessels); caudal edge (1 cm caudal to the axillary vessels); medial edge (the ribcage); lateral edge (the res major muscle); anterior edge (the pectoralis major muscle); posterior edge (chest wall and intercostal muscles).*Axilla level II* In the incidental arm, nodes will be contoured as part of the procedure whereas, in the control group, this will be hidden to not influence the dosimetric planning. The limits will be the cranial edge (5 mm cranial to the axillary vessels); caudal edge (caudal edge of pectoralis minor muscle); medial edge (the medial border of the pectoralis minor muscle); lateral edge (the lateral border of the pectoralis minor muscle); anterior edge (the anterior surface of the pectoralis minor muscle); posterior edge (chest wall and intercostal muscles).*Axilla level I* In the incidental arm, nodes will be contoured as part of the procedure whereas, in the control group, this will be hidden to not influence the dosimetric planning. The limits will be the cranial edge (1 cm below caput humeri); caudal edge (free edge of pectoralis major muscle); medial edge (the lateral border of the pectoralis minor muscle); lateral edge (the medial edge of the dorsolateral muscle); anterior edge (the plane defined by the anterior surface of the pectoralis major and minor lateral dorsal); posterior edge (the anterior surface of the subscapularis muscle).*Internal mammary chain* Nodes will be contoured in both arms and will be hidden to not influence the dosimetric planning. The limits will be the cranial edge (cranial edge of rib 1); caudal edge: (cranial edge of rib 5); medial edge (the edge of the sternum); lateral edge (5 mm lateral of internal mammary vessels or 2 cm from the edge of the sternum); anterior edge (dorsal surface of m. pectoralis major, dorsal surface of the sternum); posterior edge (pleura).*Organs at risk* The delineation of ipsilateral lung and heart is mandatory for the calculation of dose-volume histograms. The ipsilateral lung must be outlined as a single structure, and care should be taken not to include any airways; the CT must cover the entire lung volume. The heart must be outlined as a single structure to the extent of the pericardial sac; the major blood vessels (superior and inferior) are excluded and the superior extent may be simplified by identifying the vessels superior to the heart. Contralateral breast, contralateral lung, oesophagus, caput humeri, thyroid and spinal cord may be delineated according to institutional protocols.

Enlarging all volumes by adding a 5–10 mm margin in all directions to create the planning treatment volume (PTV) is recommended.

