#### Dose prescription

All doses prescribed will follow the International Commission on Radiation Units and Measurements guidelines. A minimum of 95% of the volume must receive at least 95% of the prescribed dose. Less than 5% of the volume may receive a dose of 105% and less than 2% should receive a dose of 107%, with a maximum overall dose of 110%. The dose in the breast must be 50.0 Gy by 25 fractions of 2.0 Gy in 5 weeks or through hypofractionated schedules as 40.05 Gy in 15 fractions of 2.67 Gy for 3 weeks. In the tumour bed, the schedule and total dose are left to the centre’s criteria. In node areas, the intentional irradiation to the breast and tumour bed will be calculated. Limiting doses for the organs at risk must be: (1) ipsilateral lung: V20 less than 25%; and (2) heart: V20 less than 10% and V40 less than 5%.

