#### Sample size estimation

A total of 1.400 patients must be recruited to show the non-inferiority of the experimental arm (incidental irradiation) with an 80% of statistical power when we assume a 5-year recurrence rate of 15% in the control arm (intentional irradiation) [8], a 5% non-inferiority margin, a yearly dropout rate of 5%, and a fixed sample design. Despite the short follow-up period, the large number of patients to be included in the study will preserve the statistical significance of the survival rates and will be enough to evaluate differences in the toxicity rates.

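### The contouring section hides the nodal contours in the control (intentional) arm, where the planning section requires plans that cover those nodes; the arm labels are most likely wrong

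*Protocol article*

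**What the plan says.** The Volume contouring section of the protocol article opens with a rule for everyone: the nodal areas "must be contoured in all patients regardless of the assigned arm". It then takes the volumes one by one. For the supraclavicular fossa it says: "In the incidental arm, nodes will be contoured as part of the procedure whereas, in the control group, this will be hidden", and gives the reason that the contours should not steer the plan. The same arm labels recur for axillary levels III, II and I. For the internal mammary chain the rule is the same in both arms: "Nodes will be contoured in both arms and will be hidden to not influence the dosimetric planning".

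The Treatment planning section, under node areas, sets what the plan must achieve. For control: "In the control group, the treatment planning must be optimized to ensure that the nodal areas receive the prescribed dose", with the internal mammary chain excepted. For the other arm: "In the experimental group, treatment planning for nodal areas is not performed". It adds: "The internal mammary chain will not be irradiated intentionally in any case".

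The Sample size estimation section says which arm is which. It places the assumed recurrence rate of "15% in the control arm (intentional irradiation") and calls incidental irradiation the experimental arm. The Study design section agrees on treatment: the intentional arm receives axillary and supraclavicular irradiation, and the incidental arm receives breast and tumour bed only.

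**The concern.** Because every patient is contoured, the four arm-specific sentences settle only one thing: in which arm the planner may use the nodal contours and in which arm they are kept out of view. As printed, they are out of view in the arm whose plans must reach the nodes, and in view in the arm whose plans must not aim at them.

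This is a treatment instruction in an open-label trial at over 40 sites in three countries. If a site followed it, nodal dose could fall in the control arm. In the incidental arm, the safeguard against planning towards the nodes would be missing. The arms could then become more alike. In a non-inferiority trial, a weaker contrast between treatments favours a non-inferiority conclusion. Nodal dose is also a secondary endpoint in its own right.

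**Working it through.** No sample size, event count or error rate enters this point, so there is no plan figure to reproduce. The check sets the sections side by side.

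**Step 1: which arm is control.** Sample size estimation equates control with intentional irradiation and experimental with incidental irradiation. In Volume contouring, the control group is set against the incidental arm, so there too it can only be the intentional arm. Treatment planning uses control in the same sense.

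**Step 2: compare the rules, for the supraclavicular fossa and axillary levels I to III.**

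| Arm | Treatment (Study design) | Nodal planning (Treatment planning) | Contours (Volume contouring) |
|---|---|---|---|
| Intentional = control | Nodes irradiated | Plan optimised to give the nodes the prescribed dose | Hidden from planning |
| Incidental = experimental | Breast and tumour bed only | None | Part of the procedure |

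**Step 3: can both rules be followed?**
- *Control arm:* no. A contour that must not influence the plan cannot also be what the plan is optimised to cover. Nor could coverage be checked during planning against the Dose prescription rule, "A minimum of 95% of the volume must receive at least 95% of the prescribed dose", if that rule is read as applying to every prescribed volume.
- *Incidental arm:* yes, strictly. A planner can see the nodes and still not plan for them. What is lost is the safeguard of hiding them.

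**Step 4: which direction was meant?** The internal mammary chain is intentionally irradiated in neither arm and is hidden in both. Hiding is therefore the treatment given to nodes that are not targets. The axillary and supraclavicular nodes are non-targets only in the incidental arm, so that is where they should be hidden. With both labels swapped, the contouring text agrees with Study design, Treatment planning, Sample size estimation and the internal mammary rule.

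**Step 5: extent.** Five nodal volumes are described: supraclavicular, axilla III, axilla II, axilla I and internal mammary chain. Four carry the conflicting labels (4/5). Four sentences separate the arms, and all four conflict (4/4). The one remaining volume is consistent.

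**Step 6: how the slip arose.** This cannot be told. All four sentences pair the incidental arm with the control group, and the words intentional and experimental do not occur in the section. Replacing incidental with intentional alone would not help, because the sentence would then contrast the intentional arm with the control group, which are the same arm.

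**The case against.** The strongest reply is that the intended treatment is clear from the rest of the article. Study design, Treatment planning and Sample size estimation agree with one another, and a reader comparing them would spot the slip. Randomisation, the primary endpoint, the sample size and the analysis do not depend on these four sentences. The article is a condensed account, and the 451 patients recruited from February 2015 to February 2020 were enrolled before it could have guided their planning. Whether the full protocol or the site instructions carry the same wording cannot be seen. All of this stands, and it is why no harm is claimed. It does not make the printed rule right: 1,400 − 451 = 949 patients were still to be recruited on that status.

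A second reply concerns the direction of bias. In the incidental arm, a planner who sees the nodes might cover them or spare them, and nodal planning is excluded there in any case. A site obeying Treatment planning would also have to reveal the contours in the control arm. This stands too: convergence of the arms is a possibility, not a prediction.

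A third reply is that the planning section permits high tangents and anterior-posterior fields, which can be set up without optimising on a contour. That softens the practical impossibility. It does not reconcile the texts, because a rule that the nodes must not influence the plan still conflicts with a rule that the plan must ensure their dose. The coverage argument rests on reading the Dose prescription rule as covering nodal volumes, and the conflict holds without it.

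Finally, four occurrences of one repeated sentence measure repetition rather than impact. That is fair, and the count is offered only to show where corrections are needed.

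**Conclusion.** The concern holds. Volume contouring contradicts Treatment planning for 4 of 5 nodal volumes, and no reading of the arm names removes the conflict. That the labels, rather than the planning rule, are wrong is an inference, but it is the only direction consistent with the other sections and with the handling of the internal mammary chain.

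The number of plans affected, which may be zero, and any effect on nodal dose or on the error rate of the non-inferiority test cannot be derived from the article. The point should be fixed because it is an operational treatment rule that is wrong as written, not because the trial's result has been shown to be at risk.

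**What to change.** In the supraclavicular and the three axillary paragraphs, state that the contours are drawn and used for planning in the intentional (control) arm, and drawn but kept hidden from the planner in the incidental (experimental) arm. Change both labels, and name each arm both ways so the mapping is explicit. Leave the internal mammary paragraph as it is. Check the full protocol and the site planning instructions for the same wording.

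Optionally, tabulate the nodal doses already collected in the eCRF by arm and site, without outcome data, to confirm that the arms separated. At sites with few patients such a table can reveal a reversed or absent dose contrast, but not a small shift.

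The cost is four sentences and a document check. No extra patients, procedures or data are needed.
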